## Objectives

This current protocol describes a feasibility study using a cluster randomized controlled trial (c-RCT) design. The pilot study compares implementation as usual for mental health services to the SCAPE-U implementation strategy, in which PWLP collaborates in training primary care workers and community health workers, as well as conducting home visits to service users and their families. The pilot and feasibility study have the following objectives (see Table 1):To assess the feasibility and acceptability of involving people with lived experience of psychosis in mental health trainings and home visits.To determine recruitment and retention rates of SCAPE-U facilitators, service users and their caregivers, primary care workers, and community health workers.To establish the acceptability and feasibility of data collection procedures.To demonstrate the feasibility of trial procedures.To demonstrate the ethics and safety of the study procedures.To describe changes in outcome measures at individual, family, and health system levels.To determine the cost of the SCAPE-U implementation strategy.

**Table 1 Tab1:** Feasibility trial objectives

**Objective**	**Resear**ch questions	**Hypothesis**	**Methods**	**Participants**
**1. Feasibility and acceptability of SCAPE-U**	Is it feasible to train and involve people with lived experience of psychosis in the intervention? Do primary care workers, community health workers and caregivers of service users find it acceptable to have people with lived experience of psychosis as co-facilitators in their trainings/supervision and home visits?	People with lived experience of psychosis can be trained to deliver training and home visits effectively and safely All the key stakeholders of the intervention will find the involvement of people with lived experience acceptable	Qualitative interviews Process notes Adverse event logs (target: fewer than 20% among recruited PWLE)	SCAPE-U facilitators, primary care workers, community health workers, service users and their families, research staff and trainers

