**2. Recruitment and retention**	Can we recruit, train, and retain enough PLWP to be SCAPE-U facilitators? Can we recruit and retain sufficient primary care workers, community health workers and service users and their caregivers for outcome assessment?	PLWP can be adequately recruited, trained, and retained for delivering the SCAPE-U intervention For primary care workers, community health workers and service users and their families, maximum recruitment might be required to address loss to follow-up and drop-out	Process output: number of SCAPE-U facilitator recruited, completed training, and retained. Target = 50% retention For primary care workers, community health workers: number in health posts, number completing the training, supervision and completing outcome measures. Target for both = 60% at 8 months follow-up For SU and families: 50% completing the 5 session home visits	SCAPE-U facilitators, primary care workers, community health workers, service users and their families, research staffs
**3. Acceptability and feasibility measures and data collection procedures**	Are the quantitative and qualitative assessment measures and collection procedure acceptable and feasible to administer with the stakeholders at planned intervals?	The selected measures will be acceptable and feasible for measuring the intended outputs of the study	Tool completion rate, time, missingness of data (target: fewer than 20%)	Primary care workers, community health workers, service users and families, research staff
**4. Randomization**	Is cRCT feasible to run the study and measure the intended outcomes—in terms of contamination, fidelity, and implementation strategy?	Cluster randomization is feasible to execute the study and measure intended outcomes	Baseline summary of two arms Demographic details of primary care workers, community health workers (age, gender, years of experience, qualifications, education) Record on participant’s arm crossover (target: less than 30%)	Primary care workers, community health workers, service users and families, research staff

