### Study participants

This study will involve six categories of study participants:(i)People with lived experience of psychosis trained as SCAPE-U facilitators—8 to 10 people with lived experience of psychosis who have previously received services from YouBelong Uganda [33, 35] will be recruited. The inclusion criteria are (1) diagnosis of a psychotic disorder confirmed by a mental health professional (psychiatric clinical officer or psychiatrist). (2) Capacity to provide informed consent. The main exclusion criterion is any health, functional, or cognitive impairment, assessed through mental state examination, that could jeopardize their full and safe participation in SCAPE-U activities. There are no inclusion/exclusion criteria relating to current engagement in treatment.(ii)Primary care workers—two primary care workers will be selected per health facility, with a target of 36 primary care workers per arm (72 total for the study). There are no exclusion criteria.(iii)Community health workers—we will select up to five community health workers from each health facility. This will equate to approximately 90 community health workers per arm and an estimated total of 180 community health workers for the study.(iv)Psychiatrists, psychiatric clinical officers,and psychiatric nurses—1 psychiatrist, 3 psychiatric clinical officers, and 2 psychiatric nurses who are involved in delivering training to primary care workers will be included.(v)Service users diagnosed with psychosis by primary care workers—the primary intended beneficiaries of study interventions are service users receiving treatment for psychosis at primary care facilities. The goal is to have 10 service users per cluster, 30 per arm, and 60 in total for the study. *Inclusion criteria*: (1) persons diagnosed with psychosis at a primary health care facility in Kampala/Wakiso District, following mhGAP training as part of the SCAPE-U trial; (2) ability of the service users to consent to study enrollment and procedures, or, if the service user does not have capacity to consent, a responsible surrogate can give consent; (3) persons eligible for outpatient management of psychosis. *Exclusion criteria*: (1) persons diagnosed with psychosis requiring inpatient management; and (2) persons for whom consent for participation in the study cannot be obtained.(vi)Family members of service users—at least one primary carer for study service users will be identified to collect outcome data from a family perspective (*n* = 30 per arm, 60 for the total study).

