### Measures/outcomes for feasibility criteria and other objectives

The primary outcome of this trial is to understand the feasibility and acceptability of the SCAPE-U intervention. We have developed a set of quantitative and qualitative measures to do this as guided by recommendations from pilot study reporting [49]. These measures will determine what components of the SCAPE-U intervention will be included, excluded, or modified in the future full trial. The following quantitative criteria have been set to determine if this feasibility trial can be scaled up for a fully powered trial.Recruitment: at least 2 primary care workers were recruited in the study from each of the 36 health facilities selected.Retention: 50% of SCAPE-U facilitators retained by the end of PhotoVoice training, 60% of primary care workers, 60% of community health workers retained in post until the end of the 8 months follow-up period, and 50% of service users and families retained by the end of 5 session home visits.Contamination: less than 20% of cross-arm movement of primary care workers, community health workers, service users, and their families during the 8-month follow-up period.Cluster comparison: measuring baseline characteristics of recruited primary care and community health workers across both arms. We will collect information on primary care workers and community health workers’ education qualifications, gender, prior mental health training, age, and years of experience and determine balance between arms.Data collection procedure: less than 20% of missingness in collected data.Safety: fewer than 20% of adverse events among recruited SCAPE-U facilitators and service users.

Our qualitative criteria for this feasibility study are presented in Table 3.

**Table 3 Tab3:** Assessment of feasibility and acceptability of the intervention and trial procedures

Domains	Research questions	Methods
Feasibility and acceptability of SCAPE-U intervention	Do psychiatrist/psychiatric clinical officer, primary care workers, and mental health service users find it feasible and acceptable for PhotoVoice trained people with lived experience to participate as co-facilitators in training and supervision?	● Qualitative interviews with psychiatrist/psychiatric clinical officer, primary care workers, SCAPE-U facilitators, and research staff ● Process notes from trainings and supervision sessions

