Fidelity and contagion of intervention	Can fidelity be feasibly and reliably assessed using a fidelity checklist? What degree of fidelity to SCAPE-U is achievable? Can contamination be captured through fidelity and other assessments?	● Qualitative interviews with psychiatrist/psychiatric clinical officer trainers, primary care trainees, SCAPE-U facilitators, and research staff ● Process notes and fidelity checklist from trainings and supervision sessions ● Logs of health workers and service users’ movement across arms
Ethics and safety of trial	Does the research pose harm to primary care workers, service users, or SCAPE-U facilitators, and are these harms adequately prevented, documented, and addressed?	● Qualitative interviews ● Service Users Collaboration Checklist ● Process evaluation notes ● Monitoring of adverse events

*Qualitative data* will be collected from PWLP, primary care and community health workers, service users, and their families, mental health specialists involved in training and research staff involved in data collection through key informant interviews (KIIs) and focus group discussions (FGD). We will conduct KIIs with 75% of the PWLP recruited to be SCAPE-U facilitators and who have completed PhotoVoice training and co-facilitated health workers training and home visits during two timepoints—after the health workers training and after home visits. For those who are just part of the PhotoVoice training, we will conduct an FGD talking about their experiences with PhotoVoice. For PCWs and VHTs, we will conduct KIIs with 15% of the total trained population. Selection will be based on gender, performance based on supervision notes, the number of mental health cases attended, and the level of health facility. We will interview them at 3 months post-training, i.e., during the first supervision. Twenty percent of the service users and their families receiving home visits will be interviewed after the completion of all five sessions. Finally, during the study’s end phase, we will interview all the trainers in both arms and research assistants involved in SCAPE-U data collection.

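### The service-user and family interviews give no interview point to those who stop or decline the home visits, though half the intervention arm could stop with the retention criterion still met

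*Protocol article*

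**What the plan says.** The section Measures/outcomes for feasibility criteria and other objectives states the primary outcome: "The primary outcome of this trial is to understand the feasibility and acceptability of the SCAPE-U intervention". It adds that the measures developed for this purpose will settle which parts of the intervention go forward, are removed or are changed in the full trial.

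Table 1 (Objectives), objective 1, asks whether "caregivers of service users find it acceptable to have people with lived experience of psychosis as co-facilitators" in training, supervision and home visits. Its hypothesis is that "All the key stakeholders of the intervention will find the involvement of people with lived experience acceptable". The listed methods are qualitative interviews, process notes and adverse event logs, and service users and their families are among the listed participants.

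The qualitative data paragraph gives the sampling rule for this group: "Twenty percent of the service users and their families receiving home visits will be interviewed after the completion of all five sessions".

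The retention target appears twice. Table 1, objective 2, has "For SU and families: 50% completing the 5 session home visits", and the list of quantitative criteria has "50% of service users and families retained by the end of 5 session home visits".

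The number of users is set under Study participants: "The goal is to have 10 service users per cluster, 30 per arm, and 60 in total for the study". For families, "at least one primary carer for study service users will be identified to collect outcome data from a family perspective", with 30 per arm. Under Interventions, Home level, only the intervention arm receives home visits.

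**The concern.** The interview is tied to an event, the end of the fifth session, that some participants will never reach. Those who stop after a visit or two, and those who decline, are the people best placed to say what did not work. They may have stopped because they did not want a visitor with lived experience, or for unrelated reasons such as relapse, admission or moving away. Only they and their families can say at first hand which it was.

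At stake is the decision that the trial is meant to inform. If many users stop, the retention figure will show it, but the interviews would come from people for whom the visits worked well enough to finish. The team would know how many left without hearing from them why, and so would have less to go on in changing the home-visit component.

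**Working it through.** **Inputs from the Protocol article**
- Users per cluster: 10; clusters per arm: 3 (Study participants; Study design).
- Retention target for the home visits: 50% (Table 1, objective 2; list of quantitative criteria). The two wordings are taken as one criterion.
- Interview fraction: 20% of those receiving visits, after all five sessions (qualitative data paragraph).

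**Step 1: size of the arm.** 10 × 3 = 30 users, which reproduces the stated 30 per arm. One carer per user gives 30 families.

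**Step 2: how many can stop with the criterion still met.** 30 × (1 − 0.50) = 15 users, with their families. If the criterion is missed, the number is larger.

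**Step 3: number of interviews.**
- Fraction taken of all 30: 0.20 × 30 = 6 users.
- Fraction taken of completers only, at 50% completion: 0.20 × 15 = 3 users.

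The text does not say which denominator applies. If the stated time point governs, the number interviewed who stopped early is 0 under either.

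**Step 4: what a draw from everyone would give.** Suppose 6 users were drawn at random from all 30, of whom 15 had stopped.
- Expected number who had stopped: 6 × 15/30 = 3.
- Chance of drawing none: C(15,6)/C(30,6) = 5,005/593,775 = 0.0084, or 0.8%.

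So a sample with no one who stopped would be very unlikely to arise by chance. It would follow from the sampling rule.

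**Step 5: is there another direct source?**

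| Place | What it offers on acceptability to users and families |
|---|---|
| Table 1, objective 1 | Interviews, process notes, adverse event logs; no separate route for those who stop |
| Table 3, acceptability row | Interviews with specialists, primary care workers, facilitators and research staff; users and families not listed |
| Table 4 | Symptoms, quality of life, stigma, inclusion, hospitalization, costs and caregiver impact; no acceptability measure |
| Qualitative data paragraph | The 20% interview after five sessions |

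The last row is the only described interview in which users and families speak for themselves about the visits.

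**The case against.** The strongest reply is that the phrase about five sessions fixes timing and not eligibility. The sampling frame is those receiving visits, and neighbouring sentences also attach time points to each group. Where the authors make completion a condition, for facilitators, the same paragraph says so. This reading is possible. It still leaves no interview point for someone who never has a fifth session, so the sentence needs repair on either reading.

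A second reply is that those who stop are not lost to the primary outcome, and this stands. They count directly against the retention criterion. Process notes and adverse event logs may record them, facilitators are interviewed after home visits and give feedback in supervision, and research assistants are interviewed at the end. A reader might therefore infer too much by saying that the whole acceptability result rests on completers. The documents support only the narrower statement that the first-hand account of those who stopped or declined is not collected.

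Three other strong inferences should be resisted.
- A reader might put a figure on an upward bias in an acceptability rate. The plan estimates no such rate: interviews are coded for themes (Qualitative data), and none of the listed numeric criteria is an acceptability proportion.
- A reader might treat every stop as a rejection of the visits. The documents do not say why people stop, and clinical or practical reasons are just as possible.
- A reader might see the focus group for people who take part only in the PhotoVoice training as a drop-out interview that users are denied. The text does not describe those people as drop-outs.

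Finally, this is a condensed article, and an interview guide may say more. The article is not silent here, however. It states both the fraction and the time point, and the time point causes the gap.

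**Conclusion.** The point holds in a limited form. As written, the service-user and family interviews provide no interview point for those who stop early or decline, and up to 15 of 30 intervention-arm users could stop with the retention criterion met. The consequence is a missing first-hand account for a group that may be as large as the group of completers. It is not a measurable bias in the primary outcome.

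The figures assume that the arm recruits its 30 users and that all are offered visits. If completion is well above 50%, fewer people are affected, though their accounts remain just as useful for revising the intervention. The change should be made because it costs little and bears on a question that the trial sets itself. It does not threaten the trial's validity.

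**What to change.** Reword the sampling sentence in the qualitative data paragraph so that it:
- keeps the 20% fraction, about 6 users and their families, but defines it over all intervention-arm users and families offered home visits;
- selects purposively, so that some who stopped early or declined are included where they exist, with no fixed quota;
- places the interview after the fifth session, or when visits stop, or at the scheduled 4-month assessment;
- reports themes separately for completers and non-completers.

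The number of interviews need not rise. People who stopped are harder to reach and may decline the interview too, so attempts and refusals should be recorded. Contact details are taken at consent (Recruitment), and users have assessments scheduled at 4 and 8 months (Table 4), so there are existing occasions to approach them.

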**Table 5 Tab5:**
[figure not shown]
Participant timeline

*t0* pre-[LE1] PhotoVoice, *t1 *post-[LE2] PhotoVoice, *t2*[LE3] mhGAP/community health worker pre-training, *t3*[LE4] mhGAP/community health worker post-training,* t4**[LE5] * service user enrollment, *t5*[LE6] 4-month post-enrollment,* t6*[LE7] 8-month post-enrollment *t7*[LE8] study close out

## Data analysis

### StataCorp LLC

Quantitative data will be exported to Stata 18 for statistical analysis where it will be analyzed per objective [63]. Data will be presented using frequency tables and figures. For continuous outcomes we will report means and standard deviations (or medians and with interquartile ranges, where data are skewed) and for categorical outcomes we will report raw counts (number, %) by treatment arm and overall. We will estimate intra-cluster correlation coefficients to inform the design of a subsequent fully powered trial.

We will calculate descriptive statistics (mean, standard deviations) for all quantitative outcomes, and these will be used to conduct power analyses for a subsequent definitive trial. Baseline data will be explored for comparability between treatment arms to guide future randomization and recruitment strategies.

Change in psychosis symptoms as a secondary outcome will be measured using PANSS scores summarized using means (SD) or medians (IQR), as appropriate based on distribution, at baseline, month 4, and month 8 within each arm. Mean and percentage changes from baseline to month 8, along with corresponding between-arm differences, will be presented with 95% confidence intervals to assess precision and potential effect size. Estimates will be obtained using analysis of covariance (ANCOVA) and mixed-effects linear regression, with health facility modeled as a random effect to account for clustering. Where PANSS scores are skewed, log transformation will be applied prior to analysis. Change analyses will be restricted to participants with at least one post-baseline assessment (modified intention-to-treat population).

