**Methods:**

This pilot cluster randomized controlled feasibility trial will randomize 36 health facilities to a standard implementation arm where primary care workers (PCW) will be trained by mental health specialists (control), or a collaborative care model with added co-facilitation of PCW trainings by PWLP as well as home visits by PWLP to service users (intervention). The intervention condition is referred to as “Strengthening CAre in collaboration with People with lived Experience of psychosis in Uganda” (SCAPE-U). The 36 health facilities will be distributed across six clusters with three clusters in each arm. PhotoVoice will be used to train PWLP to be co-facilitators of PCW training and provide home-based support to service users in the intervention arm. The primary outcomes of the feasibility trial will be the feasibility, acceptability, and safety of collaborating with PWLP. Data will also be collected on individual-level outcomes for PCWs, and service users to inform the feasibility of data collection and obtain effect size estimates.

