### Study design

The design is a cluster-randomized controlled feasibility trial comparing the standard implementation arm, where PCWs will be trained by mental health specialists, versus the intervention arm, where, in addition, PWLP will cofacilitate the PCWs training and provide home visits to the service users with psychosis.

The unit of randomization is a geographic cluster of primary care facilities. There are 36 primary care facilities in the two study districts. These will be divided into six geographic clusters based on a health subdistrict, each consisting of six primary care facilities. Three geographic clusters will be randomly allocated to the control arm and three to the SCAPE-U arm. We chose a cluster design because the interventions are delivered at a primary care facility and community level, meaning individual randomization is not possible. Having multiple health workers and primary care facilities in each cluster also ensures that we will not lose the entire cluster in the scenario that primary care workers or community health workers retire or are relocated by the government.

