### Randomization and blinding

Randomization of clusters in the feasibility trial will be completed prior to participant recruitment and will be conducted by an independent statistician using Stata. Covariate-constrained clusterrandomisation will be used to assign health facility clusters to study arms while ensuring balance across key variables {Hemming, 2023 #120}[48]. Covariate-constrained randomization is a form of restricted randomization; specifically, the randomization will be constrained on two characteristics: number of health facilities per arm, and rural vs. urban location.

Constrained randomisation helps prevent baseline imbalances that can occur by chance, particularly in studies with a limited number of clusters, such as feasibility trials [48]. For logistical reasons, research assistants/data collectors will not be blinded. PCWs and CHWs will be blinded to the arm allocation. We will have separate mhGAP-IG trainers for each arm, and these will be blinded. Because SCAPE-U facilitators will be engaged only in the intervention arm, and only service users accessing care at PHCs in the intervention arm will receive the home visit intervention, they will both be blinded by the cluster randomized nature of the trial.

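### The PANSS model takes health facility as its only clustering level, although six geographic clusters are randomised, so its 95% interval will be too narrow to the extent that those clusters differ

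*Protocol article*

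**What the plan says.** The Study design section fixes the randomised unit: "The unit of randomization is a geographic cluster of primary care facilities". It gives the structure, "These will be divided into six geographic clusters based on a health subdistrict, each consisting of six primary care facilities", and the allocation, "Three geographic clusters will be randomly allocated to the control arm and three to the SCAPE-U arm". The Randomization and blinding section agrees: "Covariate-constrained clusterrandomisation will be used to assign health facility clusters to study arms while ensuring balance across key variables".

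The Study participants section sets recruitment: "The goal is to have 10 service users per cluster, 30 per arm, and 60 in total for the study".

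The Data analysis section treats PANSS change as a secondary outcome. It reports changes and between-arm differences with 95% confidence intervals, to convey precision and possible effect size. The estimates come from ANCOVA and "mixed-effects linear regression, with health facility modeled as a random effect to account for clustering". An earlier paragraph of the same section adds: "We will estimate intra-cluster correlation coefficients to inform the design of a subsequent fully powered trial". It does not say at which level.

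**The concern.** Arm varies only between the six geographic clusters, so the information about the arm effect is limited by how much those six clusters differ. A model whose only random effect is the facility treats about 18 facilities per arm as separately allocated, when three clusters per arm are. Variation between clusters is spread over 18 units instead of 3 and mostly drops out of the standard error.

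The facility term cannot make up for this. With 60 service users over 36 facilities there are on average 1.67 users per facility, so facility variance is hard to separate from residual error.

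The intervals are meant to show precision, and the ICC is meant for the full trial. If the between-arm difference looks more precise than it is, or the ICC belongs to a level that will not be randomised, the planning inputs are weakened.

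**Working it through.** The article gives no ICC and no precision figure for PANSS, so there is no stated figure to reproduce. The one precision figure in the Sample size section concerns a participation proportion and does not bear on this point.

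**Inputs from the article.** Six clusters, three per arm; six facilities per cluster, so 18 per arm; 10 users per cluster, so 30 per arm.

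**Assumptions.** Geographic-cluster ICC rc from 0 to 0.20; additional facility ICC rf = 0 unless noted; all 60 users followed; limits of ±1.96 for the facility model. Total variance of the baseline-adjusted outcome is set to 1, so results are in SD units of that outcome.

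**Variance of the arm difference**

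- With the cluster component: V_true = 2[rc/3 + rf/18 + (1 − rc − rf)/30]
- As a facility-only model sees it: V_fac = 2[(rc + rf)/18 + (1 − rc − rf)/30]

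At rc = 0.05 and rf = 0:

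- V_true = 2[0.05/3 + 0.95/30] = 0.0967, SE 0.311
- V_fac = 2[0.05/18 + 0.95/30] = 0.0689, SE 0.262
- Ratio 1.185, so coverage = 2Φ(1.96/1.185) − 1 = 90.2%

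**Simulation.** 2,000 runs per setting, with the 10 users of each cluster spread at random over its six facilities. A baseline-adjusted REML model with a facility random intercept and ±1.96 limits was compared with baseline-adjusted cluster means on t with 6 − 2 = 4 df (critical value 2.776). Monte Carlo error near 95% is √(0.95 × 0.05/2000), about 0.5 percentage points.

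| Cluster ICC | True SE | Facility-model SE | Ratio | Coverage, formula | Coverage, simulated facility model | Coverage, simulated cluster means, 4 df |
|---|---|---|---|---|---|---|
| 0 | 0.258 | 0.258 | 1.00 | 95.0% | 94.6% | 94.9% |
| 0.01 | 0.270 | 0.259 | 1.04 | 94.0% | 94.5% | 94.3% |
| 0.02 | 0.280 | 0.260 | 1.08 | 93.1% | 92.9%* | 94.7%* |
| 0.05 | 0.311 | 0.262 | 1.19 | 90.2% | 90.9% | 95.7% |
| 0.10 | 0.356 | 0.267 | 1.34 | 85.8% | 85.2% | 94.4% |
| 0.20 | 0.432 | 0.275 | 1.57 | 78.8% | 78.8% | 95.0% |

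*Simulated with rf = 0.02 as well. Adding rf = 0.05 at rc = 0.05 gave 90.2% for the facility model, so extra facility variance changes little.

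**How little the facility term tells.** The mean estimated facility ICC was 0.06 when no clustering existed at either level, and 0.11 when the cluster ICC was 0.10.

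**A geographic-cluster random intercept with 4 df** was also simulated. It was conservative: coverage was 99.5% at rc = 0, 99.2% at 0.05, 97.7% at 0.10 and 96.3% at 0.20.

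**Precision of a cluster-level ICC.** For 6 clusters of 10 and an ICC of 0.05, the large-sample SE is (1 − 0.05)(1 + 9 × 0.05)√(2/(10 × 9 × 5)) = 0.95 × 1.45 × 0.0667 = 0.09. That is larger than the ICC itself.

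**The case against.** The strongest case on the other side is about importance. The primary outcomes are feasibility, acceptability and safety, PANSS is secondary, and the Sample size section rules out a power calculation and formal testing. None of the quantitative criteria for going on to a full trial uses the PANSS interval. The Data analysis section also feeds means and standard deviations into the later power analyses, and the choice of random effect does not alter those. All of this stands and limits the harm. It does not remove it, because the intervals are offered as a statement of precision.

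Four stronger readings are tempting but not supported:

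- **That the ICC will be at facility level.** The article does not say. Elsewhere it uses the word cluster for the geographic unit, so the randomised level may be intended. Facility level is only an inference from the single clustering term named.
- **That an ANCOVA ignoring clustering is planned.** The sentence can equally describe one baseline-adjusted mixed model. On either reading, geographic cluster is absent.
- **That a correct interval is 1.7 times as wide.** At an ICC of 0.05, 2.776 × 0.311 = 0.86 SD against 1.96 × 0.258 = 0.51 SD does give 1.7. However, 2.776/1.96 = 1.42 of that comes from a critical value the article never states, only √1.45 = 1.20 comes from omitted cluster variance, and the comparator ignores clustering altogether.
- **That the abstract contradicts the design.** It says the trial "will randomize 36 health facilities to a standard implementation arm", but its next lines place those facilities in six clusters, three per arm. This is loose wording.

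A reader might also argue that facilitators and supervision are shared across clusters. The article documents only separate trainers for each arm, and the point does not need more.

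**Conclusion.** The mismatch of levels is certain: the article randomises geographic clusters and models facilities, and nothing else in it repairs this. The consequence for the interval is conditional. A reader might infer that the intervals are too narrow whatever the data show, but with no variance between geographic clusters the facility model covers close to 95%. The loss is small up to an ICC of about 0.02 (93%) and material from about 0.05 (91%, then 85% at 0.10). These figures rest on assumed ICCs, ±1.96 limits and the planned 10 users per cluster.

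This should be fixed, but it does not threaten the trial's primary purpose. It bears on the stated precision of one secondary outcome and on inputs to the full trial.

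**What to change.** In the Data analysis section, replace the facility-only random effect with a baseline-adjusted analysis at geographic-cluster level, in one of two forms:

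- a random intercept for geographic cluster, with facility nested within it if estimable, fitted by REML with a small-sample degrees-of-freedom correction such as Kenward-Roger or Satterthwaite; or
- an analysis of baseline-adjusted cluster summaries on 4 df.

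The second form held nominal coverage in the simulation. The first, with 4 df imposed, was conservative at low ICCs. The Kenward-Roger and Satterthwaite corrections were not simulated.

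If ANCOVA is meant as a separate model, say so and make it account for geographic cluster too. State that the ICC is reported at geographic-cluster level with its confidence interval, and treat it as very imprecise with six clusters.

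The cost is one paragraph of wording and no new data. The downside is wider intervals.
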